### Data Management and Monitoring

Upon recruitment, the participants’ identities will be replaced with numerical codes to safeguard their privacy. Data collection will be conducted at baseline, week 4, and week 8. This process will entail the involvement of 2 proficient data specialists who will be responsible for transcribing the paper-based records into a unified database while meticulously verifying the accuracy of the entered data. Ultimately, both the paper records and encrypted electronic files will be securely stored and redundantly backed up by the research leader. These records will be retained in storage for a period of 3 years following the conclusion of the study.

The oversight of the study will be carried out under the purview of the ethics committee of the Shanghai Municipal Hospital of Traditional Chinese Medicine. Importantly, the members of this committee have been carefully vetted to ensure they possess no conflicts of interest pertaining to this study. The principal investigators will retain unfettered access to all study results and will have the final authority to decide on the termination of the study. Furthermore, they will extend the privilege to project team members to disseminate the trial’s findings through the publication of research papers.

### Statistical Analysis

The collected data will meticulously be entered into Microsoft Excel (Microsoft Corporation), and subsequent statistical analysis will be conducted using SPSS software (version 18.0; SPSS Inc). Continuous variables will be summarized using the mean value and SD, with the median and IQR used for variables exhibiting nonnormal distributions. Categorical variables will be presented as frequencies or percentages.

For within-group comparisons, paired 2-tailed *t* tests will be used. Between-group differences will be analyzed through 2-sample, independent-sample *t* tests, with effect sizes computed using Cohen *d* statistics. Furthermore, demographic characteristics, baseline measurements, and changes in measurements from baseline to study completion between the 2 groups will be analyzed using 2-sample, independent-sample *t* tests. In cases where baseline measurements exhibit disparities, analysis of covariance will be implemented to account for these variations when comparing the 2 groups.

The clinical overall efficacy evaluation will be based on a nonparametric test for 2 independent samples. In instances of limited participant numbers within a specific subject or in the presence of missing data, the Mann-Whitney *U* test will be used to assess differences between the groups. A statistical significance level of *P*<.05 will be used, signifying statistical significance when this threshold is met.

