### Outcomes

#### Primary Outcome (PSQI)

The primary outcome is the change in PSQI from baseline to week 8. The PSQI is a comprehensive self-report instrument comprising 19 items aimed at evaluating sleep quality and disturbances experienced within a 1-month time frame. These items collectively contribute to the generation of 7 distinct “component” scores, encompassing assessments of subjective sleep quality, sleep latency, sleep duration, habitual sleep efficiency, sleep disturbances, use of sleeping medication, and daytime dysfunction. The sum of the scores derived from these 7 components yields a singular global score. The total global score spans a range from 0 to 21, with a lower global score indicative of a higher quality of sleep [28].

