### Sample Size

The following 2 hypotheses are related to the differences between the 2 groups:

Hypothesis 1: μ_1_= μ_2_Hypothesis 2: μ_1_≠ μ_2_,

where μ_1_ is the PSQI mean score of the 8-week treatment in the BDJQG group, and μ_2_ is the PSQI mean score of the 8-week treatment in the CBTI group.

The required sample size has been calculated using an estimation formula based on the difference between 2 sample means and SDs (PSQI, which is assessed using composite points of sleep quality). Therefore, in a study with this sample size, the difference between the BDJQG group and the CBTI group will be considered, and the conservative comparison method by Bonferroni will be adopted. In this study, it is expected that the BDJQG group will be 1.78 points better than the CBTI group in the PSQI scale mean score. The final calculated difference and SD of the 2 groups of the PSQI mean scores were calculated [40]. On the basis of 0.9 power to detect a significant difference (α=.025; 1-sided), 34 participants will be required for each group.

The following formula was used to calculate the sample size in this trial:

[figure not shown]

Given that an attrition rate of ~20% is anticipated, our target enrollment will be 43. Therefore, a total of 86 participants should be recruited for this RCT.

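### Baseline PSQI is adjusted for only when an undefined disparity is seen; ANCOVA fixed in advance would be at least as powerful under equal SDs and would remove the data-dependent choice

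*Protocol article*

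**What the plan says.** All references are to the protocol article.

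- Primary Outcome (PSQI): "The primary outcome is the change in PSQI from baseline to week 8".
- Statistical Analysis, on the tests: "demographic characteristics, baseline measurements, and changes in measurements from baseline to study completion between the 2 groups will be analyzed using 2-sample, independent-sample *t* tests". One set of t tests therefore serves both the baseline comparison and the outcome comparison.
- Statistical Analysis, on adjustment: "In cases where baseline measurements exhibit disparities, analysis of covariance will be implemented to account for these variations when comparing the 2 groups". No threshold or criterion for a disparity is given, and no other section names baseline PSQI as a covariate for the primary comparison.
- Sample Size: "it is expected that the BDJQG group will be 1.78 points better than the CBTI group in the PSQI scale mean score", with 34 per arm for 0.9 power at one-sided α = .025, raised to 43 per arm for about 20% attrition. The SD is not printed. The hypotheses are written on week-8 scores: μ1 "is the PSQI mean score of the 8-week treatment in the BDJQG group".

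**The concern.** Allocation is random, so any baseline difference between arms is due to chance. Whether adjustment helps depends on how strongly baseline PSQI predicts week-8 PSQI, and a baseline comparison carries no information on that.

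The rule has three consequences:

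1. The primary model is not known until baseline data have been inspected. Because the criterion is undefined, two analysts could choose differently from the same data.
2. When the rule is not triggered, the analysis is a t test on change. That fixes the baseline coefficient at 1, where ANCOVA would estimate it, and this costs precision.
3. When r is below 1 (equal SDs), subtracting the whole baseline over-corrects a chance imbalance. The arm that starts worse appears to improve more through regression to the mean.

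At stake are some of the trial's power and the accuracy of the estimate in trials with moderate imbalance that was not flagged.

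**Working it through.** **Inputs.** From the Sample Size section: difference 1.78, one-sided α = .025, power 0.9, 34 per arm evaluable, 43 per arm enrolled. One-sided .025 corresponds to the two-sided P<.05 in Statistical Analysis. Assumptions, because the article does not give them: the SD, the correlation r (shown at 0.3, 0.5 and 0.7), equal SDs at baseline and week 8, and a trigger of P<.05 on the baseline t test.

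**The plan's own figure.** n = 2(1.960 + 1.282)² SD² / 1.78². Setting n = 34 gives SD = 2.26, and any SD from about 2.23 to 2.26 rounds up to 34. Attrition: 34 / 0.8 = 42.5, so 43 per arm and 86 in total, as stated. With the t distribution, power at SD 2.26 and 34 per arm is 0.89; the normal approximation gives 0.90.

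**Precision.** With a common score SD s:
- SD of change = s√(2(1 − r))
- residual SD in ANCOVA = s√(1 − r²)
- variance ratio, ANCOVA to change = (1 + r)/2, which is 0.65, 0.75 and 0.85 at r = 0.3, 0.5 and 0.7.

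**Reading A: 2.26 is the SD of the week-8 score.** At r = 0.3 the SD of change is 2.26 × √1.4 = 2.67 and the ANCOVA SD is 2.26 × √0.91 = 2.16. Simulated power (50,000 trials per scenario, 34 per arm):

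| r | t test on change | plan's two-step rule | ANCOVA always |
|---|---|---|---|
| 0.3 | 0.772 | 0.785 | 0.915 |
| 0.5 | 0.891 | 0.899 | 0.955 |
| 0.7 | 0.985 | 0.986 | 0.993 |

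The trigger fires in about 5% of trials, so the two-step rule recovers little of the loss.

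**Reading B: 2.26 is the SD of change.** The t test has power 0.89. The ANCOVA SD is 2.26 × √((1 + r)/2) = 1.82, 1.96 and 2.08, giving power of about 0.98, 0.96 and 0.93. By the normal formula, the n for 0.9 power falls from 34 to 23, 26 and 29 per arm.

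**Overall type I error of the two-step rule.** 0.042, 0.042 and 0.046 at r = 0.3, 0.5 and 0.7, against a nominal 0.05.

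**Unflagged imbalance.** The largest baseline gap that is not significant at P<.05 is t(.975) × √(2/n):
- 34 per arm: 1.997 × √(2/34) = 0.48 SD, or 1.09 points at SD 2.26
- 43 per arm: 1.989 × √(2/43) = 0.43 SD, or 0.97 points.

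The resulting shift in the change contrast is (1 − r) × gap. At r = 0.5 this is 0.55 or 0.48 points, which is 31% or 27% of 1.78. (Readings A and B coincide at r = 0.5, since √(2 × 0.5) = 1.)

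Among null trials with a baseline t between 1.5 and about 2.0, the change-score test rejects in 0.113, 0.094 and 0.085 of cases at r = 0.3, 0.5 and 0.7, against about 0.05 for ANCOVA. Allowing for simulation variation, about 7 to 12% is a fair range.

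**The case against.** **Baseline is not ignored.** It enters every analysis through the change score, and a flagged disparity would get ANCOVA. This stands. What remains is over-correction of imbalance that is not flagged.

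**The planned test is valid.** A reader might infer that choosing the model after a baseline look inflates false positives, or that the 7 to 12% rejection rate describes the trial. The documents and the calculation do not support this. Under randomisation the t test on change is unbiased on average, and overall type I error is at or slightly below nominal. The higher rate holds only for a selected minority of trials with near-threshold imbalance. Blinded statisticians (Randomization and Blinding) also limit any choice of model that favours one arm.

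**The P<.05 trigger is inferred.** The article gives no criterion; the inference rests on the baseline t tests in the same paragraph. The two-step simulation and the maximum unflagged gap depend on it. If the trigger is instead a judgement, the model choice is less predictable, and its operating characteristics cannot be calculated.

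**The power shortfall is not established.** A reader might conclude that the stated 0.9 fails because the hypotheses are on week-8 scores and the endpoint is change. That follows only if the unprinted SD is that of scores and r is below 0.5 with equal SDs. If it is the SD of change, 0.9 roughly holds. The difference of 1.78 is unaffected, since under randomisation both contrasts have the same expected value.

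**Equal SDs may not hold.** Entry is limited to ISI 8 to 21, which could narrow baseline spread. If the baseline SD were 0.7 of the week-8 SD (an assumption), power for change against ANCOVA is about 87% vs 92% at r = 0.3 and 95% vs 96% at r = 0.5. The shift at r = 0.5 falls to about 0.19 points. This reduces the gain and does not favour the conditional rule.

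**Conclusion.** The point holds as one of efficiency and prespecification, not of validity. That the article states an undefined, data-dependent covariate rule is certain from its text. The size of the cost is conditional on the assumed SD, r, equal SDs and trigger. Under those assumptions the power given up is about 13 percentage points at r = 0.3 (0.915 − 0.785), 6 at r = 0.5 and under 1 at r = 0.7 if 2.26 is the week-8 SD. If it is the SD of change, the gain from ANCOVA over the t test is about 9, 7 and 4 points (from 0.89). Conditional on a near-threshold unflagged imbalance, the estimate can be off by about a quarter to a third of the planning difference at r = 0.5. With equal SDs the variance ratio (1 + r)/2 is below 1 for any r below 1, so ANCOVA gains under either reading of the SD. The change should be made, but its absence would not invalidate the trial.

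**What to change.** Replace the conditional sentence in Statistical Analysis with a single rule: the primary comparison is an ANCOVA of week-8 PSQI (or change in PSQI) on arm and baseline PSQI, whatever the observed balance. With baseline in the model, the two forms give the same treatment estimate. Analyse each continuous secondary outcome likewise, with its own baseline value as covariate. Drop the between-arm significance tests of baseline measurements and demographics, and describe baseline by arm only.

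The cost is a sentence or two. Table 1 already schedules PSQI at baseline for all participants, so no visit, measurement or recruitment changes. The Results section places analysis at the end of data collection, so the amendment should be dated and fixed before any outcome comparison by arm. It would also help to state the planning SD and whether it refers to week-8 scores or to change, so that the 0.9 power can be checked against the analysis used.

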**Methods:**

A randomized controlled trial will be conducted on 86 patients, who will be divided into a BDJQG group and a cognitive behavioral therapy for insomnia group at a ratio of 1:1. Interventions in both groups will be given to the participants 7 times a week for 8 weeks, and the participants will be followed up for 4 weeks. The primary outcome is the change in the Pittsburgh Sleep Quality Index from baseline to week 8. The secondary outcomes are the changes in the Hyperarousal Scale, Insomnia Severity Index, Fatigue Scale-14, wrist actigraphy, salivary cortisol level, and functional magnetic resonance imaging from baseline to week 8. All main analyses will be carried out on the basis of the intention-to-treat principle.

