### Study Setting

Participants will be recruited from the Shanghai Municipal Hospital of Traditional Chinese Medicine. Eligibility for inclusion will be determined by 2 orthopedic surgeons based on predefined inclusion and exclusion criteria. Participants who are determined to be eligible and provide written informed consent will be randomly allocated to either the BDJQG group or the CBTI group in a 1:1 ratio. The BDJQG group will undergo BDJQG treatment, while the CBTI group will receive cognitive behavioral therapy for insomnia. Both groups will undergo an 8-week-long treatment program, consisting of 1 supervised session per week at Shanghai University of Traditional Chinese Medicine and the remaining 6 days of the week completed at home. The study will span a total of 13 weeks, comprising a 1-week-long screening period, an 8-week-long treatment phase, and a subsequent 4-week-long follow-up period.

Assessments using various scales will be conducted at baseline, the 4-week intervention mark, the 8-week intervention mark, and the 4-week follow-up. SCL will be measured at baseline, the 4-week intervention mark, and the 8-week intervention mark. Actigraphy and fMRI assessments will be administered at baseline and the 8-week intervention mark. Figure 1 gives a visual representation of the research process, and Table 1 shows an overview of the study’s time points.

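### The stated response to missing data, a switch to the Mann-Whitney U test, does nothing about missing outcomes and should be replaced by an analysis of all randomised participants

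*Protocol article*

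**What the plan says.** All from the protocol article:

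- Primary Outcome (PSQI): "The primary outcome is the change in PSQI from baseline to week 8".
- Statistical Analysis, second paragraph: "Between-group differences will be analyzed through 2-sample, independent-sample *t* tests". Analysis of covariance is added if the arms differ at baseline.
- Statistical Analysis, third paragraph: the overall clinical efficacy evaluation uses a nonparametric two-sample test. Then, for small numbers or missing values, "in the presence of missing data, the Mann-Whitney *U* test will be used to assess differences between the groups". No other response to missing outcomes is described.
- Abstract, Methods: "All main analyses will be carried out on the basis of the intention-to-treat principle".
- Ethical Considerations: data collected before a participant withdraws are kept and enter the final analysis.
- Sample Size: "On the basis of 0.9 power to detect a significant difference (α=.025; 1-sided), 34 participants will be required for each group", and "Given that an attrition rate of ~20% is anticipated, our target enrollment will be 43".
- Study Setting: "Assessments using various scales will be conducted at baseline, the 4-week intervention mark, the 8-week intervention mark, and the 4-week follow-up".

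**The concern.** The choice between a t test and a Mann-Whitney test concerns the shape of the distribution. Neither test can use a participant whose outcome was not observed. A rule that changes the test because data are missing therefore leaves the missing-data problem as it was.

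Three things are at stake.

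1. **Intention to treat.** As stated, the rule compares participants with an observed outcome. The PSQI that dropouts gave at baseline and week 4 has no place in a two-sample test of change to week 8.
2. **The estimate.** If the rule reaches the primary outcome, a rank test replaces the comparison of means on which the sample size rests. It gives no mean difference in PSQI points and cannot carry the covariate adjustment that the same section plans. Which test is run would also depend on whether any value turns out to be missing.
3. **Bias.** The trial is open-label and the primary outcome is self-reported. If dropout depends on response and differs by arm, the observed-case comparison is biased under either test.

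**Working it through.** **Step 1: the plan's own figures.** The planned difference comes from Sample Size: "it is expected that the BDJQG group will be 1.78 points better than the CBTI group in the PSQI scale mean score". With one-sided α = 0.025 and power 0.9, n per group = 2 × (1.960 + 1.282)² × SD² / 1.78². The article states no SD. An n of 34 is obtained for an SD of about 2.23 to 2.26; with 2.26, n = 2 × 10.51 × 5.108 / 3.168 = 33.9, so 34. The SD of 2.26 used below is therefore an assumption backed out of the plan. The inflation is correct: 34 / (1 − 0.20) = 42.5, so 43 per group and 86 in total.

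**Step 2: how often the rule applies.** 86 × 0.20 = 17.2 participants without a week-8 PSQI, and 86 × 0.80 = 68.8 with one (34.4 per arm). With about 17 missing values expected, the condition is all but certain to be met.

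**Step 3: does switching tests help?** Simulation with no true difference: 43 per arm, normal outcome, SD 2.26, two-sided 0.05, 6000 runs, observed values only. Outcome-related dropout depends on the participant's own outcome plus random noise of equal variance. The difference is the second arm minus the first, and a negative value favours the second arm.

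| Dropout, first vs second arm | Mean difference | Mann-Whitney rejects | t test rejects |
|---|---|---|---|
| 20% vs 20%, random | 0.01 | 5.2% | 4.9% |
| 20% vs 20%, outcome-related | 0.01 | 4.7% | 4.8% |
| 10% vs 30%, outcome-related | −0.48 | 14.6% | 15.5% |
| 5% vs 35%, outcome-related | −0.74 | 28.6% | 29.3% |

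The two tests behave almost identically, so switching removes essentially none of the bias. It also costs little power: with a true difference of 1.78 and 20% random dropout, power was 87.4% for Mann-Whitney and 88.5% for the t test.

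**Step 4: size of the bias on the primary outcome.** Assumptions: SD 2.26 at each visit; correlation .5 between baseline and each later visit, and .7 between weeks 4 and 8; no true effect; about 28% outcome-related dropout in one arm and random dropout in the other. The SD of the change is then 2.26 × √(2 × (1 − .5)) = 2.26. Observed-case bias in PSQI change, favouring the arm with outcome-related dropout:

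- Dropout driven by a poor week-4 PSQI *level*: about −0.06 to −0.22.
- Dropout driven by a poor week-4 *change*: about −0.2 to −0.75.

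Within each range, the size depends on how tightly dropout follows week-4 status. A very weak link gives less still, for example −0.03 in the first case. Against the planned 1.78 points, the range is 0.06/1.78 = 3% to 0.75/1.78 = 42%.

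**Step 5: does using the earlier PSQI help?** In a separate run (4000 runs, 43 per arm, SD 2.26, dropout 27% vs 10%), the observed-case bias in change was −0.42 when week-4 change drove dropout and −0.13 when week-4 level did. An estimate that used baseline and week-4 PSQI brought both to about 0. That is expected here, because missingness depended only on observed data.

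**The case against.** The strongest reply has five parts.

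- **The article never says that only completers are analysed.** A Mann-Whitney test fits intention to treat if dropouts receive values or ranks, and such detail is often left to an analysis plan. A reader might infer that the article plans a completers-only analysis and will ignore the week-4 PSQI. It states neither, and Ethical Considerations points the other way for withdrawn participants' data. What remains is that the one response the article does state cannot by itself keep either promise.
- **The rule may not govern the primary outcome.** It follows directly after the sentence on overall clinical efficacy, while changes from baseline are assigned to t tests in the paragraph before. The ambiguity is real, so the point about a displaced primary test is conditional. Also, the primary outcome is itself a change score, so baseline is not ignored altogether.
- **Dropout is already allowed for.** For numbers, yes: 43 per arm is right. Enrolment does not remove bias.
- **Unequal dropout is not shown.** A reader might infer it from very different demands in the two arms. The Abstract and Study Setting describe the same frequency and the same split of supervised and home days in both arms. The intervention sections describe the arms differently, but no arm-specific dropout rate is given. Unequal dropout is a possibility, not a finding.
- **The rank test adds no bias of its own.** Correct: Step 3 shows it is about as biased as the t test and no worse. The fault is that it is offered as the answer to missing data when it is not one.

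**Conclusion.** The point stands as a wrongly chosen rule, not as missing detail. The article names a test as its response to missing data, and that test does not respond to missing data. With about 17 of 86 outcomes expected to be missing, the rule will almost certainly be invoked. Read as covering all between-group comparisons, it replaces the t test, yields no mean difference in PSQI points or covariate adjustment, and does not by itself deliver intention to treat.

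The bias is a range that depends on assumptions: about −0.06 to −0.75 points on PSQI change with roughly 28% outcome-related dropout in one arm only, and near zero if dropout is equal across arms or unrelated to outcome. Its sign reverses if the outcome-related dropout falls in the other arm. The SD, correlations, dropout split and mechanism are all assumed, so no single value within the range should be quoted as the expected bias.

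**What to change.** Before the data are analysed:

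1. Delete the rule that ties the Mann-Whitney test to missing data. If a rank test is kept for the overall efficacy evaluation, say so and confine it to that.
2. Make the primary analysis a likelihood-based mixed model for repeated measures on all randomised participants as allocated. The outcome is the PSQI at the scheduled post-baseline visits (weeks 4, 8 and 12 in Table 1). Terms are arm, visit, arm-by-visit, baseline PSQI and baseline-by-visit, with unstructured covariance. Report the week-8 contrast in PSQI points with its 95% CI as the primary result.
3. Add a simple delta-shift sensitivity analysis: worsen the unobserved week-8 values by increasing amounts, separately by arm, and report where the conclusion changes.

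Other methods that use the earlier PSQI, such as multiple imputation, would also serve. No extra visits or participants are needed, because the PSQI is already scheduled at these times and the planned software family can fit the model. The cost is revised wording, some extra analysis work, and reliance on a missing-at-random assumption, which the sensitivity analysis is there to probe.
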